## Product manufactured

The *T. fagifolia* Mart. extract will be combined with calcium alginate and cashew gum. After weighing, the sample will be dissolved in distilled water and subjected to solubilization. In the next step, the mixture will be measured, transferred to a container, and the solvent will be evaporated in an oven, with an average incubation time of 24 to 36 h at 40 °C. The process will be completed in a biological safety cabinet, where the sample will be sterilized using ultraviolet light, and the dressings will be stored in surgical paper and sealed. The product development process is protected by patent.

## Intervention

### Control group

The wounds will initially be cleaned with saline solution and sterile gauze. During all sessions, both the therapist and the patient will wear protective eyewear. Treatment will be performed twice a week, totaling 20 sessions over 10 weeks. The probe will be positioned perpendicularly to the ulcer, allowing precise irradiation of the wound edges. In the internal area of the wound, the sweeping technique will be applied, in which the probe will be moved slowly over the entire surface of the ulcer in continuous, parallel movements, maintaining an approximate distance of 1 cm. The duration of each session will be automatically determined by the device based on predefined energy density parameters. At the end of each application, the ulcer will be covered with a conventional dressing, defined in this study as standard wound care consisting of sterile gauze associated with topical *Helianthus annuus* vegetable oil. Patients will be instructed to clean the wound and change the dressing daily, following standardized home aseptic care guidelines [27]. To ensure protocol standardization, all sessions will be performed by the same trained therapist, using the same equipment, application method, and parameters described in Table 1.

### Intervention groups

DFUs will undergo standardized cleaning with isotonic saline solution, using aseptic technique and sterile gauze. After cleaning, group G1 will receive topical application of *T. fagifolia* Mart. extract, followed by sterile occlusion of the lesion according to the established protocol. In group G2, *T. fagifolia* Mart. extract will be applied after irradiation with PBM Endophoton KLD GaAs (904 nm, 70 mW, dose of 10 J/cm²), followed by sterile occlusion of the wound with sterile gauze. Treatment will be conducted twice a week, totaling 20 sessions over 10 weeks. To ensure protocol standardization, all sessions will be performed by the same trained therapist. Participants will be instructed to remove the previously applied extract at the end of the day, then clean the lesion with isotonic saline solution, and apply occlusion with a conventional dressing consisting of sterile gauze and *Helianthus annuus* vegetable oil on days without treatment sessions. A detailed description of the procedures applied to each group can be found in Table 2.

**Table 1 Tab1:** Photobiomodulation parameters of the Endophoton KLD device used in the protocol

Parameters	PBM 904 nm	Description
Operational mode	Continuous	Device Settings
Radiant power (mW)	70 mW	Device Settings
Full power (W)	0,07 W	Device Settings
Contact area (cm^2^)	0,001 cm^2^	Device Settings
Power density (W/cm^2^)	1,00 W/cm^2^	Device Settings
Pulse duration	100 × 10^− 9^s	Device Settings
Time (s)	2s	Device Settings
Energy density (J/cm^2^)	10 J/cm^2^	Device Settings
Application technique	Scan and point	No skin contact
Irradiated area	-	Dependent on the size of the ulcer area
Number and frequency of sessions	20 sessions twice a week	-

**Table 2 Tab2:** Description of therapeutic procedures in intervention groups

Procedure	Group G1 T. fagifolia extract	Group G2 PBM + T. fagifolia extract
Initial ulcer cleansing	Isotonic saline solution + aseptic technique + sterile gauze	Isotonic saline solution + aseptic technique + sterile gauze
Therapeutic application	Topical application of *T. fagifolia* Mart extract	GaAs 904 nm, 70 mW, 10 J/cm², followed by topical application of *T. fagifolia* Mart extract.
Irradiation technique	—	Probe perpendicular to the edges; scanning inside the ulcer; distance ≈ 1 cm
Wound occlusion	Sterile dressing	Sterile dressing
Frequency of sessions	2x/week	2x/week
Total sessions	20 sessions (10 weeks)	20 sessions (10 weeks)
Home care	Remove the extract at the end of the day, clean the lesion with saline solution, and cover it with a *Helianthus annuus* oil dressing.	Remove the extract at the end of the day, clean the lesion with saline solution, and cover it with a *Helianthus annuus* oil dressing.

### Primary outcome

#### Ulcer reduction rate

The primary variable will be the rate of ulcer size reduction over 10 weeks. After the initial assessment, the DFUs will be identified, and the area will be photographed alongside a paper ruler, which will serve as a calibrator for the ImageJ software (Fig. 2) [28, 29]. DFUs will be assessed at three time points: pre-intervention (baseline), after 5 weeks (10 sessions), and after 10 weeks (20 sessions). The calculation of the reduction rate will follow the same parameters used by Ahmed and Irfan [30], represented by the formula: $$\:\frac{Af-Ai}{Ai}\:x\:100$$. Here, Ai and Af denote the initial and final ulcer areas, respectively. Ulcer area measurements will be performed by a blinded independent evaluator, who will be unaware of group allocation. The primary outcome will be compared between groups and across time points using repeated-measures analysis.

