### Sample size

The sample size was calculated using G*Power 3.1.9.4 software, based on the primary outcome of wound area reduction [25]. A repeated-measures ANOVA (F-test) was used to account for the interaction between within-subject factors (three time points: baseline, 5 weeks, and 10 weeks) and between-subject factors (three groups: CG, G1, and G2). The analysis considered a statistical power of 0.90, an alpha level of 0.05, and an effect size of 0.31. Based on these parameters, a total sample size of 93 participants was estimated. Assuming a 10% loss to follow-up, 102 volunteers will be recruited (34 volunteers per group).

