### Secondary outcomes

#### Clinical response analysis

A clinical responder analysis will be performed considering a 50% wound healing threshold, based on previously published evidence from our group and analyzed according to Farrar et al. [22, 31]. The cumulative proportion of clinical responders will be estimated across groups. For graded outcomes, the mean difference between response curves will be used to calculate the absolute risk reduction (ARR), from which the number needed to treat (NNT = 1/ARR) will be derived, providing a clinically meaningful interpretation of treatment efficacy. These outcomes will be compared between groups.

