### Data monitoring

This is the first clinical trial to evaluate the topical application of *T. fagifolia* Mart. extract in ulcers, providing initial data on its safety in humans. All procedures related to ulcer assessment, extract application, and adverse event reporting will be prospectively recorded using standardized forms. Safety monitoring will include active and systematic surveillance of local reactions at the lesion site (erythema, pain, pruritus, increased exudate, and signs of infection), as well as systemic adverse events potentially associated with the intervention. All events will be documented, classified according to severity and causality, and managed in accordance with predefined clinical protocols. Serious or unexpected adverse events will be promptly reported to the Research Ethics Committee, in compliance with current national regulations.

Participants will be monitored at each treatment session for signs of secondary infection throughout the study. At each session, lesions will be systematically assessed by a trained evaluator for clinical indicators of infection, including purulent exudate, malodor, dark discoloration, tissue necrosis, perilesional cellulitis, and systemic signs such as fever. The diagnosis of infection will follow the criteria established by the Infectious Diseases Society of America (IDSA) [33], requiring the presence of at least two local signs of inflammation or infection. In cases where infection is suspected or confirmed, the participant will be promptly referred to an independent physician, not involved in the intervention, for appropriate clinical management. The intervention protocol may be adjusted or discontinued if clinically indicated to ensure patient safety (Table 3).

**Table 3 Tab3:** Recruitment, interventions, and assessment schedule according to the recommendations for interventional trials (SPIRIT)

STUDY PERIOD							
	Enrollment		Post-allocation (weeks)				Post-intervention
TIMEPOINT	Recruitment	Allocation	Basiline	5 W	10 W	Once a week	t_x_
ENROLLMENT:							
* Recruitment*	X						
* Selection Criteria*	X						
* Allocation*		X					
INTERVENTIONS							
* CG*			X	X	X		
* G1*			X	X	X		
* G2*			X	X	X		
ASSESSMENTS:							
* Evaluation form*			X				
* Ulcer reduction rate*			X	X	X		
* Clinical Response Analysis*			X	X	X		
* Glycemic level assessment*			X			X	
* University of Texas Rankings*			X	X	X		

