### Statistical analysis

All statistical analyses will be conducted according to the intention-to-treat principle. Data will be tabulated in spreadsheets (Excel package) and analyzed using SPSS version 29 (Statistical Package for the Social Sciences). Sociodemographic data will be presented as descriptive statistics, absolute values and percentages, or mean and standard deviation (median and interquartile range). Normality will be assessed using the Kolmogorov–Smirnov test. The chi-square test will be applied for categorical data. To analyze differences between groups, a one-way ANOVA or the Kruskal–Wallis test will be performed. Intragroup analysis will be conducted using one-way repeated-measures ANOVA or the Friedman test. Statistical significance will be set at *p* < 0.05, and results will be presented in tables. The cumulative proportion of responders will be calculated considering a 50% healing rate, based on the article previously published by the group, and analyzed as described by Farrar et al. [22, 31]. In studies with graded outcomes, the mean difference between the curves of two groups represents the absolute risk reduction (ARR), from which the number needed to treat (NNT = 1/ARR) can be derived.

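### The primary outcome is named a reduction but its formula gives percent change with the opposite sign, and it is scheduled at baseline, where it is 0 for every participant

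*Protocol article*

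**What the plan says.** All references are to the protocol article.

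- **Ulcer reduction rate (Primary outcome).** "The primary variable will be the rate of ulcer size reduction over 10 weeks". The printed formula is (Af-Ai)/Ai x 100, and "Here, Ai and Af denote the initial and final ulcer areas, respectively". On timing: "DFUs will be assessed at three time points: pre-intervention (baseline), after 5 weeks (10 sessions), and after 10 weeks (20 sessions"). On analysis: "The primary outcome will be compared between groups and across time points using repeated-measures analysis".
- **Table 3 (Data monitoring).** The row "Ulcer reduction rate" is marked at baseline, 5 weeks and 10 weeks, and so is the row for the clinical response analysis.
- **Clinical response analysis.** "A clinical responder analysis will be performed considering a 50% wound healing threshold".
- **Statistical analysis.** "The cumulative proportion of responders will be calculated considering a 50% healing rate". Neither this section nor the previous one gives a sign convention, refers back to the printed formula, or defines another measure of healing.
- **Sample size.** The calculation is based on wound area reduction, with a within-subject factor of "three time points: baseline, 5 weeks, and 10 weeks", three groups, effect size 0.31, power 0.90 and alpha 0.05. It gives 93 participants, raised to 102 for 10% loss.

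**The concern.** There are two separate defects in the definition of the primary outcome.

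**Sign.** For a quantity called a reduction, larger should mean better. The printed formula runs the other way: its best possible value is -100, and any positive value is an ulcer that has grown. The label and the formula cannot both be followed. What is at stake is the direction in which results are reported and any rule that puts a threshold on the quantity. The 50% responder rule, the cumulative responder curves, and the absolute risk reduction and number needed to treat derived from them all depend on direction.

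**Baseline.** At baseline the current area is the initial area, so the rate is fixed at 0 by construction. Treating it as one of three repeated measurements gives the model a level without variance, and correcting the sign does not cure this. The formula's second term is also described as the final area, although the rate is to be computed at week 5 as well.

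**Working it through.** **1. The printed formula at example areas.** Inputs: the formula and its two symbols from the primary outcome section. The areas are illustrative, with Ai = 10 cm².

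| Area at visit (cm²) | Printed: (Af-Ai)/Ai x 100 | Reversed: (Ai-Af)/Ai x 100 |
|---|---|---|
| 0 (healed) | -100 | +100 |
| 4 | -60 | +60 |
| 5 (halved) | -50 | +50 |
| 10 (unchanged, or baseline) | 0 | 0 |
| 15 (grown by half) | +50 | -50 |
| 16 | +60 | -60 |

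On the printed scale, a value of at least 50 requires (Af-Ai)/Ai ≥ 0.5, that is Af ≥ 1.5 x Ai. Only growing ulcers qualify. On the reversed scale the same cut-off requires Af ≤ 0.5 x Ai, which is what a 50% healing rule means.

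**2. Effect of the sign on the tests.** Multiplying every value by -1 changes no sum of squares and only reverses ranks. The p-values of the ANOVA, Kruskal-Wallis, repeated-measures ANOVA and Friedman tests named in the statistical analysis section are therefore the same under either sign.

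**3. The baseline level.** Let y5 and y10 be the rates at weeks 5 and 10. The baseline rate is (Ai-Ai)/Ai x 100 = 0 for everyone, under either sign.

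- A one-way ANOVA of the rate at baseline is 0/0, and no participant can be a responder there.
- A participant's mean over three levels is (0 + y5 + y10)/3, which is 2/3 of the mean of y5 and y10. Rescaling by a constant leaves F unchanged, so the between-groups test is exactly the test on weeks 5 and 10 alone. The comparison survives, but the third level adds nothing.
- Variances cannot be equal across time, because the first is 0. The three variances of differences that sphericity requires to be equal are Var(y5), Var(y10) and Var(y10 - y5). They coincide only if the two post-baseline variances are equal and their correlation is exactly 0.5.

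**4. The plan's sample size.** The article gives no correlation between measurements (rho). For a between-groups test over m measurements, lambda = f² x N x m/(1 + (m-1) x rho), with 2 and N-3 degrees of freedom and N in multiples of 3.

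- Three measurements, rho = 0.5 (assumed), N = 93: lambda = 0.0961 x 93 x 3/2 = 13.41, power 0.907. This reproduces the stated 93.
- Two measurements, N = 93: lambda = 0.0961 x 93 x 2/1.5 = 11.92, power 0.869.
- Two measurements, N = 102: lambda = 0.0961 x 102 x 2/1.5 = 13.07, power 0.901. The requirement before loss is 102.

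Range over the assumed correlation, all else equal:

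| rho | N, three measurements | N, two measurements |
|---|---|---|
| 0.3 | 75 | 90 |
| 0.5 | 93 | 102 |
| 0.7 | 111 | 117 |

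The sample-size section describes a group-by-time interaction, and no version tried of that test returns 93. With rho = 0.5 the interaction needs 30 (39 with two time points). Two other conventions for the effect size need 84 and 87 (135 and 138 with two time points). The direction of the change is the same throughout, but its size depends on choices that the article does not state.

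**The case against.** The strongest reply is that these are matters of wording. The formula is ordinary percent change, and any analyst will read -60 as a 60% shrinkage. As shown above, the sign alters no planned p-value. On baseline, the text says that the ulcers are assessed at three times, and baseline area must be measured because it is Ai. The baseline mark in Table 3 may mean only that measurement, and the three-level sample-size factor would fit an analysis of area itself. Covariate adjustment and the timing of the responder outcome are often left to an analysis plan, which is not shown.

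Much of this stands. A reader might infer from the formula that responders will be counted in reverse, so that growing ulcers are scored as successes and the number needed to treat is computed on the wrong patients. The article does not support that. It never sets an at-least-50 inequality against this formula, and an ulcer that grew cannot meet a 50% wound healing threshold on any ordinary reading. A reader might also infer that the zero baseline invalidates the group comparison, but it does not: the between-groups test is unchanged, and a multivariate group-by-time test still compares the groups on weeks 5 and 10.

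What the reply does not remove is the conflict in the stated text. The label and formula disagree, nothing says that negative means improvement, and no second healing measure is defined for the threshold to rest on. Table 3 names the rate and the responder outcome at baseline, not the area, and the outcome section says that the primary outcome is compared across time points. If area is what enters the model, the article should say so.

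**Conclusion.** The definition of the primary outcome is wrong as printed and should be corrected before analysis.

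The sign error is certain and complete: every shrinking ulcer scores negative. Its consequence is limited to reporting and to threshold rules. Misclassified responders would follow only from applying the cut-off literally to the printed scale, against the evident intent.

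The baseline problem is the more substantive of the two. If the rate is the variable analysed, as Table 3 and the outcome section indicate, one of the three planned levels is a constant and two informative time points remain. On the assumed test that reproduces 93, power at 93 falls from 0.907 to 0.869, and the requirement before loss rises to 102. That equals the full recruitment target and leaves no allowance for the 10% loss. These power figures rest on a between-groups test with rho = 0.5, neither of which the article states, so they are indicative. The zero baseline itself needs no assumption beyond the rate being the variable analysed.

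**What to change.** 1. Define reduction (%) = (Ai - area at visit)/Ai x 100, with area 0 if the ulcer has healed. Replacing the final area by the area at the visit also makes the week 5 value well defined.
2. State that a responder is a participant with a reduction of at least 50% on that scale.
3. Analyse the rate at weeks 5 and 10 only, with baseline area as covariate. Alternatively, analyse ulcer area itself at all three times and say that area is the modelled variable.
4. In Table 3, remove the baseline marks for the rate and the clinical response analysis, and show baseline ulcer area as its own entry.
5. Restate the sample-size basis for the time points actually analysed, naming the test and the assumed correlation.

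Items 1, 2 and 4 cost one formula, one sentence and a small table edit. Item 3 needs no new data, since baseline area is already measured. The real cost lies in item 5: with two time points the stated power may look less favourable (102 rather than 93 before loss, under the assumptions above), and the sponsor would have to accept that or justify the existing target on another basis.

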**Fig. 2 Fig2:**
[figure not shown]
Measuring the ulcer area with a disposable paper ruler

### Secondary outcomes

#### Clinical response analysis

A clinical responder analysis will be performed considering a 50% wound healing threshold, based on previously published evidence from our group and analyzed according to Farrar et al. [22, 31]. The cumulative proportion of clinical responders will be estimated across groups. For graded outcomes, the mean difference between response curves will be used to calculate the absolute risk reduction (ARR), from which the number needed to treat (NNT = 1/ARR) will be derived, providing a clinically meaningful interpretation of treatment efficacy. These outcomes will be compared between groups.

### University of Texas rankings

To identify changes in ulcer depth, ulcer images will be obtained before the intervention (baseline), after 5 weeks (10 sessions), and after 10 weeks (20 sessions), and classified using the University of Texas Wound Classification System [32]. Volunteers will be grouped into A1 and C1 (superficial ulcers), A2 and C2 (ulcers involving the tendon or joint capsule), and A3 (ulcers involving the bone). This classification will be used for longitudinal assessment of ulcer depth and compared between groups over time.

### Glycemic level assessment

Participants random blood glucose which will be measured levels will be monitored once per week throughout the 20 sessions using the Accu-Chek^®^ Active glucometer. Patients will be instructed to keep their arms extended alongside their bodies, in a vertical position, for approximately one minute. A puncture will then be performed using sterile lancets, and the blood sample will be applied to the device’s specific reagent strip. Glycemic levels will be analyzed to assess potential associations with wound healing and compared between groups over time.

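### Glucose is to be compared between groups over time, but the tests fixed for it give no single between-arm test over the weekly course and ignore baseline glucose

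*Protocol article*

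**What the plan says.** All references are to the protocol article.

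- **Glycemic level assessment** sets the aim: "Glycemic levels will be analyzed to assess potential associations with wound healing and compared between groups over time". Random glucose is to be "monitored once per week throughout the 20 sessions using the Accu-Chek". Twenty sessions at two per week is 10 weeks, so about 10 readings per participant.
- **Initial assessment** lists capillary glucose among the data collected at entry, and **Table 3** marks the glycemic assessment at baseline as well as weekly. A baseline value therefore exists.
- **Statistical analysis** gives the between-group method: "To analyze differences between groups, a one-way ANOVA or the Kruskal–Wallis test will be performed". It gives the over-time method separately: "Intragroup analysis will be conducted using one-way repeated-measures ANOVA or the Friedman test". Significance is set at p < 0.05.
- **Ulcer reduction rate** promises a repeated-measures comparison of groups and time points, and **Sample size** describes a group-by-time model. Both concern wound area only; neither is extended to glucose.

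**The concern.** The aim for glucose has two dimensions, arm and week. The listed methods take them one at a time. The one-way test compares arms on a single number per participant. The repeated-measures or Friedman test looks at weeks inside one arm. Three separate within-arm results do not compare the arms: a significant change in one arm and a non-significant change in another can arise from the same underlying change.

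Whoever analyses the data must therefore either run the one-way test week by week, or choose one summary (final week, mean, change) that the text does not name. The first choice inflates the chance of a spurious arm difference. The second leaves the choice open and, as listed, makes no use of baseline glucose.

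Glucose is the trial's only laboratory measure of glycaemia; Study limitations says that HbA1c is not included. The Introduction lists a hypoglycemic property among those of the species, so an isolated significant week might attract more attention than it deserves.

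**Working it through.** **Does any listed method match the aim?**

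| Listed method | Null hypothesis for glucose | Compares arms? | Uses the weekly course? | Uses baseline? |
|---|---|---|---|---|
| One-way ANOVA / Kruskal–Wallis | Arms equal on one value per participant | Yes | Only through a summary that is not named | No |
| One-way repeated-measures ANOVA / Friedman | Constant across weeks within one arm | No | Yes | Only as one more time point |

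No row answers yes in all three columns. The plan gives no figure for glucose, so there is none to reproduce.

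**Inputs for sizing.** Three arms and 93 participants before the loss allowance (Sample size), so 93 / 3 = 31 per arm. Ten weekly readings. Alpha 0.05. Assumed, because the document gives neither: equal correlation ρ between any two of a participant's readings, from 0.3 to 0.8, and unit variance at each reading.

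**1. False positives if the one-way test is run weekly.** With independent weeks the chance of at least one p < 0.05 would be 1 − 0.95^10 = 0.40. Correlation lowers it. Simulation with no arm difference gives:

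| ρ | At least one of 10 weeks significant |
|---|---|
| 0.3 | 35–37% |
| 0.5 | about 30% |
| 0.7 | 21–23% |
| 0.8 | 17–18% |

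The ranges show the spread over repeated runs. If correlation instead decays with the gap between weeks (lag-1 correlation 0.5, 0.8, 0.9), the figures are 35%, 26% and 19%. A single ANOVA of each participant's mean rejects about 5% of the time.

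**2. Power lost by leaving out baseline.** Assume that one arm differs from the other two by 0.5 SD at every week after baseline. The arm means are 0, 0 and 0.5, so the sum of squared deviations from their mean is 0.25 × 2/3 = 0.1667. The noncentrality of the F test on 2 degrees of freedom is

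λ = 31 × 0.1667 / v = 5.17 / v,

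where v is the residual variance of the quantity analysed:

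- week 10 alone: v = 1;
- mean of 10 weeks: v = ρ + (1 − ρ)/10;
- mean of 10 weeks adjusted for baseline: v = ρ + (1 − ρ)/10 − ρ².

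| ρ | Week 10: λ, power | Mean, unadjusted: v, λ, power | Mean, baseline-adjusted: v, λ, power |
|---|---|---|---|
| 0.3 | 5.2, 50% | 0.37, 14.0, 92% | 0.28, 18.5, 97% |
| 0.5 | 5.2, 50% | 0.55, 9.4, 77% | 0.30, 17.2, 96% |
| 0.7 | 5.2, 50% | 0.73, 7.1, 64% | 0.24, 21.5, 99% |
| 0.8 | 5.2, 50% | 0.82, 6.3, 59% | 0.18, 28.7, above 99% |

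Simulation with 4,000 trials per setting agrees with these powers to within about one percentage point.

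**The case against.** **Weekly testing is not prescribed.** One-way ANOVA can equally be applied to each participant's mean, final value or change, and then keeps its 5% error rate. This stands. The 17–37% applies only if the test is run week by week. What remains is that the text names no summary, that the within-group test does not fill the gap, and that the one-way test leaves baseline out whichever summary is used.

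**The Statistical analysis section is general and a condensed article leaves detail elsewhere.** It ties none of its tests to glucose and does not say that its list is complete. This stands in part. A missing detail would be no finding, but here the section states a one-way form for between-group comparisons and a within-group form for change over time. An analysis plan that followed it would inherit the mismatch.

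**A stronger reading is tempting:** that the plan cannot detect the association between glucose and healing, because no listed test of arms or weeks pairs a participant's glucose with that participant's ulcer. The documents do not support it. The Glycemic level assessment section itself plans an association analysis, and only the technique is unnamed, which is commonly left to an analysis plan. Nothing says that the arm comparison is meant to serve as the association test. "The chi-square test will be applied for categorical data" is not limited to comparisons of arms either. One can simulate a rejection rate near 5% for the arm comparison of glucose against about 83% for a correlation test when the true correlation is 0.3. That sets tests of two different null hypotheses side by side and measures no loss in this plan.

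**The consequences are speculative.** No section proposes to read a single-week difference as a treatment effect, and the hypoglycemic remark is background on the species. This is fair, and it is a reason to rate the point low.

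**Conclusion.** The point holds as a minor mismatch between a stated secondary aim and the methods fixed for it: the plan asks for a comparison of arms over time and lists no single test that makes it or that uses baseline glucose.

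Its size depends on how the gap is filled. With weekly testing, the familywise false-positive chance is about 17–37% instead of 5%. With one test of the mean, error is controlled but power is 59–92%, against 96% to over 99% with baseline adjustment; week 10 alone has about 50%. These figures rest on assumed correlations of 0.3 to 0.8, 31 participants per arm and, for power, an assumed constant difference of 0.5 SD in one arm. The document supplies neither the correlation nor the difference.

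A reader should not infer that the association analysis is absent or invalid; it is planned with its method left open. The sample size, the primary outcome and data collection are unaffected.

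**What to change.** In the Statistical analysis section, replace the one-way between-group test for glucose with one baseline-adjusted test, chosen in advance:

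- a mixed model on the weekly readings with arm, week, arm-by-week and baseline glucose, stating that the arm effect averaged over weeks is the between-group test and that arm-by-week is reported as a description of change; or
- ANCOVA of each participant's mean weekly glucose on arm and baseline glucose.

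If the first weekly reading is the baseline reading, use it as the covariate and not also as an outcome.

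An optional clarification, not a correction: name the association method, for example a regression of week-10 ulcer area on mean weekly glucose, adjusted for arm and baseline area, reported as a slope with its 95% confidence interval and labelled as association only because glucose is measured after randomisation.

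The cost is a few sentences and a little analysis in the SPSS already planned, with no new data. The small downside is that a single overall test does not identify a particular week.

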### Initial assessment

After meeting the eligibility criteria and signing the informed consent form, participants will have their lower limbs assessed by an external evaluator. A form developed by the researcher will be used to collect data such as personal information, clinical history, capillary blood glucose, body mass index (BMI), time since DM diagnosis, and ulcer duration. In addition, the exact affected area will be identified and recorded during the assessment.

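### The between-group tests named for glucose cannot make the promised comparison over time and do not use baseline glucose, which costs precision but does not cause bias

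*Protocol article*

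**What the plan says.** All references are to the protocol article.

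- **Collection.** The Initial assessment section lists glucose among the entry data ("clinical history, capillary blood glucose, body mass index (BMI"). Under Glycemic level assessment, a secondary outcome, it is "monitored once per week throughout the 20 sessions". Table 3 marks both baseline and once a week. The reading is random, not fasting.
- **Purpose.** "Glycemic levels will be analyzed to assess potential associations with wound healing and compared between groups over time". The promise at issue is the last part, that levels will be "compared between groups over time".
- **Between-group test.** The Statistical analysis section states: "To analyze differences between groups, a one-way ANOVA or the Kruskal–Wallis test will be performed". It names no covariate.
- **Within-group test.** "Intragroup analysis will be conducted using one-way repeated-measures ANOVA or the Friedman test".
- **Not stated.** The article does not say which glucose value enters the between-group test (a raw weekly reading, a change from baseline or a participant summary). It gives no effect size, standard deviation, correlation or power target for glucose. The Study limitations section says that HbA1c is not collected.

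**The concern.** The aim and the named tests do not match. A comparison of arms over time needs a method that takes group and repeated readings together. One-way ANOVA and Kruskal–Wallis compare arms on one number per participant. The repeated-measures ANOVA and Friedman tests follow time, but only inside one arm. No test on the list does both.

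The named between-group tests also leave out the baseline reading, although every participant has one. Readings from one person are usually correlated, so baseline explains part of the spread between participants, and a test without it is less precise than the data allow.

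How to collapse about ten weekly readings into a group comparison is left open. One possible route is a separate test each week at p < 0.05, which would make a chance finding considerably more likely than 5%. With no HbA1c, these readings are the trial's only glycemic evidence, and the trial wants to relate them to healing.

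**Working it through.** **The plan's own figure.** The Sample size section gives 93 participants (102 with losses) for wound area, with f = 0.31, three groups, three time points, alpha 0.05 and power 0.90. A between-groups repeated-measures F-test with an assumed correlation of 0.5 reproduces it: λ = f²·N·m/(1+(m−1)ρ) = 0.0961 × 93 × 3/2 = 13.41 on 2 and 90 df, power 0.907 (0.897 at N = 90). The figure concerns wound area, so it sets no power for glucose.

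**Inputs for the illustration.**

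- From the protocol: three groups, N = 93, alpha 0.05.
- Assumed: f = 0.20 (SD of group means over the SD of a single reading, constant over weeks); ten post-baseline readings; the same correlation ρ between any two readings, baseline included.

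**Formulas.** Power is from the noncentral F with 2 numerator df, and λ = f²·N / v, where v is the remaining variance as a share of the single-reading variance:

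- one week, unadjusted: v = 1 (90 df)
- one week, with baseline: v = 1 − ρ² (89 df)
- ten-week mean, unadjusted: v = (1 + 9ρ)/10 (90 df)
- ten-week mean, with baseline: v = (1 + 9ρ)/10 − ρ² (89 df)

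Here f²·N = 0.04 × 93 = 3.72.

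| Analysis | ρ = 0.3: v, λ, power | ρ = 0.5: v, λ, power |
|---|---|---|
| One week, unadjusted | 1; 3.72; 38% | 1; 3.72; 38% |
| One week, with baseline | 0.91; 4.09; 41% | 0.75; 4.96; 49% |
| Ten-week mean, unadjusted | 0.37; 10.05; 80% | 0.55; 6.76; 62% |
| Ten-week mean, with baseline | 0.28; 13.29; 90% | 0.30; 12.40; 88% |

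For a single week, baseline adds about 3 points at ρ = 0.3 and 11 at ρ = 0.5. For the ten-week mean it adds 10 and 26 points.

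**Sensitivity to f.** At f = 0.31, borrowed from wound area, the unadjusted single-week test has 75% power. Adding baseline gives 77% at ρ = 0.2, 79% at 0.3, 87% at 0.5 and 97% at 0.7. The unadjusted ten-week mean already has 99% at ρ = 0.3 and 95% at ρ = 0.5, and with baseline both exceed 99%.

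**Change from baseline.** For one week, λ = f²·N/(2(1−ρ)). At f = 0.31 power is 60% at ρ = 0.3, below the 75% of the unadjusted reading. It is equal at ρ = 0.5, and 94% at ρ = 0.7 against 97% with baseline as covariate.

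**Week-by-week testing.** Simulating ten correlated one-way ANOVAs with no true difference (31 per arm, 20,000 runs), the chance of at least one p < 0.05 is about 36% at ρ = 0.3, 30% at ρ = 0.5 and 22% at ρ = 0.7.

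**The case against.** A reader might infer three stronger things, and the documents support none of them.

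- **That raw glucose will be tested, week by week.** The article names tests, not the value tested. Raw readings, changes and a participant mean all fit its wording, and nothing says that ten separate tests will be run. The false-positive figures are therefore conditional.
- **That ignoring baseline loses much of the power.** This depends on an unstated correlation. For a single week at f = 0.31 the gain is only 2 to 4 points at ρ = 0.2 to 0.3, and a random reading may well correlate weakly. The rise from 75% to above 99% comes mostly from averaging ten readings. An unadjusted one-way ANOVA on participant means, which the text does not exclude, would achieve that part. There is also no planned power for glucose to lose.
- **That the comparison is biased.** Under randomisation the unadjusted comparison is unbiased, and its standard error already allows for chance baseline imbalance.

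It can also be said that glucose is only one of several secondary outcomes, that its first stated purpose is association with healing, and that covariates and the handling of weekly readings are commonly left to the full protocol or SAP. The first two hold and limit the weight of the point. The third holds for matters on which the article is silent. Here it names specific between-group tests, and they do not fit the comparison it promises. The mismatch is not peculiar to glucose: the Primary outcome and University of Texas sections also promise comparisons over time. Glucose differs in having the most repeated readings.

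**Conclusion.** The point stands as a minor, nearly free improvement. The article promises a comparison of glucose between arms over time, and the between-group tests it names neither join group with time nor use the baseline reading. The consequence is lost precision, plus multiplicity only if the tests were repeated weekly.

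The size is illustrative. With N = 93, f = 0.20, ten readings and equal correlations, baseline adjustment of the ten-week mean is worth 10 points of power at ρ = 0.3 and 26 at ρ = 0.5. For a single week it is worth about 3 and 11. The effect size, the correlations and the count of ten readings are assumptions, and none comes from glucose data in the plan. The mismatch between the two sections rests on none of them.

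**What to change.** For the glucose outcome, replace the one-way tests in the Statistical analysis section with one model. Either of these would do:

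- a linear mixed model of the weekly post-baseline readings on group, week and group-by-week, with baseline glucose as covariate and the repeated readings linked within participant; or
- an ANCOVA of each participant's mean post-baseline glucose on group and baseline glucose.

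State that one adjusted difference with its confidence interval will be reported for each pair of arms, averaged over the weeks, so that no week is singled out.

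The cost is a change of wording and one degree of freedom for the covariate. No new data are needed, and both models can be run in SPSS 29, which the protocol already names.
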